### Statistics

#### Sample size

The sample size calculation is based on log-rank test, using Simpson’s rule as implemented in Stata version 11.1 [23] to allow for the unequal length of follow-up [24]. The study duration comprises an 18-month recruitment period and a 12-month follow-up period, giving a maximum follow-up of 30 months and a minimum of 12 months. Assuming control group survival proportions of 45%, 20% and 10% at the minimum, average and maximum follow-up times respectively, a hazard ratio of 0.45 and an additional 10% loss-to-follow-up, a total of 108 patients (54 per group) are needed to ensure a power of 85% using a two-sided type I error of 5%. The control group figures are conservative estimates based on the sole randomised controlled trial of NIV, which is now considered standard care in the UK. The FDA study of DP in ALS/MND has estimated a one year survival of 86% after study entry for patients using DP and NIV (personal communication). We have estimated the sample size on a conservative (but clinically important) 1-year difference in survival of 45% versus 70%, which produces the estimated hazard ratio of 0.45. It is anticipated that we will have complete survival data on all subjects recruited, based on previous experience in MND trials. With regard to quality of life data we anticipate a low level of missing data due to loss to follow up. We have reviewed the patients who were initiated on NIV in the year up to Jun 2009 at the study sites and we have maintained contact with 100% of those patients surviving at 12 months. The appointment of a research nurse at each study site will enable home visits if necessary to collect the quality of life data. We have however allowed for a 10% loss to follow up in the sample size/power calculation.

### Data analysis

The primary outcome is overall survival, defined as the duration from randomisation to death. This will be analysed by Cox regression, with covariates including treatment group and the minimisation factors. As a secondary analysis we will also report survival separately for patients who are NIV tolerant and those who are NIV intolerant. The proportionality assumption will be assessed using time-dependent covariates and scaled Schoenfeld residuals [25]. The change from baseline for QoL outcomes will be analysed by two methods. The first analysis will compare the change from baseline at 12-months using analysis of covariance (ANCOVA) in which the treatment group and the baseline score are included as covariates along with minimisation factors. The second analysis will assess the QoL over the entire 12-month period by modelling the change from baseline by repeated measures ANCOVA with the same covariates. QoL will be summarised both with imputation for missing data (in particular, assigning a score of zero following the date of death) and without. The safety and tolerability profiles will be reported by analysing the proportion of patients experiencing adverse outcomes. A description of the statistical analysis of efficacy and safety outcomes will be written in the trial Statistical Analysis Plan by the trial statistician.

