### Method of randomisation

Participants will be randomised to either the treatment arm (n = 54) or the control arm (n = 54). Patients will be allocated their treatment by method of minimisation. The minimisation factors will be baseline bulbar function, baseline FVC, age and sex. Patient details (ID, date of birth and the factors above) will be entered into the Sheffield Clinical Trials Research Unit (CTRU) web-based randomisation system and the treatment allocation will be returned. Non-deterministic minimisation will be employed by including a random element into the allocation algorithm. The participant will be informed of their treatment allocation within a week of randomisation either by phone or letter. Please refer to Figure 2 below for the screening and randomisation process.

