### Data collection

Once participants have been enrolled and allocated their treatment the data collection process starts (Table 1). Data collection occurs at baseline, 2, 3, 6, 9 and 12 months for both groups. Additionally the DP group will undergo data collection at the time of surgery and 1 week following surgery. The subgroup of 12 participants and carers who will be undertaking the qualitative sub study will also undergo interviews at 1 and 6 months post implantation.

**Table 1 T1:** Data collection

**Data collection tool**	**Time point of study**	**When collected/given to patient**	**By who**	**Purpose**
Informed consent form	Recruitment	In clinic, face to face	Neurology or respiratory consultant	Ensure participants have been consented appropriately
Screening and eligibility assessment form	Recruitment/Screening	In clinic	Neurology or respiratory consultant or research nurse	Ensure protocol violations or deviations are avoided. Include ECG, blood gases, blood test, FVC and phrenic nerve evaluation tests
ALSFRSr	Screening	As above	As above	Allows minimisation on bulbar function
Survival	1 week, 2, 3, 6, 9, 12 months, then finally at last follow up for last patient	In clinic, telephone	Research nurse	Primary outcome measure
*EQ5D questionnaire (patient and carer)	Screening, 2, 3, 6, 9 and 12 months	In clinic or over the phone	Neurology or respiratory consultant or research nurse	QALYs, secondary outcome measure
SF36	Screening, 2, 3, 6 and 12 months	As above	As above	Generic quality of life, secondary outcome measure
Sleep Apnoea Quality of Life (SAQLI)	Screening, 2, 3, 6 and 12 months	As above	As above	Respiratory specific quality of life, secondary outcome measure
*Caregiver Burden Inventory questionnaire	Screening, 2, 3, 6 and 12 months	As above	As above	Secondary outcome measure
Side effects/ adverse event/concomitant medications and devices forms	All time points as required	As above	As above	AE/SAEs
Healthcare resource use	2, 3, 6, 9 and 12 months	As above	As above	Economic, secondary outcome measure
Patient Diary incorporating:	1 week, 2, 3, 6, 9 and 12 months	In clinic, at hospital or at home	Neurology or respiratory consultant and Patient and Carer	Main outcome Record DP and NIV use
* NIV use				
* DP use and				
* DP Parameters setting				
NIV use	Screening	As above	As above	Main outcome
Medical history and examination on CRF	Screening and 12 months	In clinic	Neurology or respiratory consultant	Eligibility for trial, safety

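### The non-bulbar part of the screening ALSFRS-R has no stated place in the primary Cox model; pre-specifying it as one covariate is a cheap, optional way to add power

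*Protocol article*

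**What the plan says.** The Data analysis section defines the outcome: "The primary outcome is overall survival, defined as the duration from randomisation to death". It then fixes the model as Cox regression, "with covariates including treatment group and the minimisation factors". Method of randomisation names the factors: "The minimisation factors will be baseline bulbar function, baseline FVC, age and sex". Table 1 (Data collection) lists the ALSFRS-R as a whole instrument at screening, with the purpose "Allows minimisation on bulbar function". No analysis mentions the total score or its non-bulbar part. Data analysis ends by leaving the full description of the efficacy analysis to a statistical analysis plan, which is not available here.

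The Sample size section uses a log-rank test and states that "a total of 108 patients (54 per group) are needed to ensure a power of 85% using a two-sided type I error of 5"%. It assumes "a hazard ratio of 0.45 and an additional 10% loss-to-follow-up" and takes no credit for covariates.

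**The concern.** In a Cox model, leaving out a baseline variable that predicts death pulls the estimated hazard ratio towards 1 and costs power, even when the arms are balanced. The article collects a functional score before allocation but gives a stated use only to its bulbar component. Minimisation on four factors also does not control chance imbalance in non-bulbar function between two arms of 54.

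If the remaining part of the score predicts death beyond bulbar function, FVC, age and sex, the primary test could be made more powerful with data already in hand. What is at stake is a possible gain in efficiency, not the validity of the planned test: type I error is near 5% with or without the score.

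**Working it through.** **1. The stated sample size.** Inputs from Sample size: two-sided 5%, power 85%, hazard ratio 0.45, 10% loss, and control survival of 45%, 20% and 10% at 12, 21 and 30 months (21 is the midpoint of 12 and 30).

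- Deaths (Freedman): (1.960 + 1.036)² × (1.45/0.55)² = 8.978 × 6.950 = 62.4.
- Control death probability (Simpson): 1 − (0.45 + 4×0.20 + 0.10)/6 = 0.775.
- Pacing arm, with each survival raised to the power 0.45: 1 − (0.698 + 4×0.485 + 0.355)/6 = 0.501.
- Mean 0.638. N = 62.4/0.638 = 97.8; divided by 0.9 this is 108.6.

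The stated 108 reproduces to within one patient, with no covariate in the calculation.

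**2. What the score could add.** The article gives no association between the ALSFRS-R and survival, so its strength is an assumption. I simulated trials of 98 evaluable patients with control survival of 45/20/10%, censoring uniform over 12 to 30 months, and one standardised covariate independent of treatment. The covariate stands for the part of the score not carried by the four minimisation factors. Each trial was analysed by Cox regression without and with it (3,000 trials per row; simulation error of each power about √(0.87×0.13/3000) = 0.6 points).

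Two readings of 0.45 were used. In A it is the hazard ratio conditional on the score. In B the unadjusted hazard ratio is held near 0.45, so the conditional one is smaller (0.442 down to 0.412).

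| Log-hazard per SD | HR per SD | A: without → with | A: gain | B: without → with | B: gain |
|---|---|---|---|---|---|
| 0 | 1.00 | 87.4 → 87.1% | −0.3 | same as A | −0.3 |
| 0.2 | 1.22 | 86.8 → 87.4% | 0.6 | 87.9 → 88.5% | 0.6 |
| 0.3 | 1.35 | 84.6 → 87.2% | 2.6 | 87.7 → 90.0% | 2.3 |
| 0.4 | 1.49 | 83.2 → 87.9% | 4.7 | 87.6 → 91.5% | 3.9 |
| 0.5 | 1.65 | 82.2 → 88.8% | 6.6 | 88.6 → 93.8% | 5.2 |

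The trials averaged 62 to 64 deaths.

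**3. Cross-checks.**

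- A separate run on the same control curve, under reading A, gave 86.3 v 86.3%, 84.0 v 84.7%, 83.9 v 86.7% and 78.3 v 85.2% at 0, 0.2, 0.3 and 0.5. The gains are 0, 0.7, 2.8 and 6.9 points.
- A run with four other covariates in the model and 97 patients gave gains of −0.7, 1.2, 2.3 and 5.5 points at the same strengths. It used an exponential control curve through 45% at 12 months. That curve implies about 25% and 14% survival at 21 and 30 months, not the plan's 20% and 10%, so its power levels are not the plan's. Its gains agree with the others.

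Across all runs the gain is about 0 to 3 points up to 0.3 per SD and about 4 to 7 points at 0.4 to 0.5. With no residual prognostic value the loss is at most 0.7 points, which is within simulation error.

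**The case against.** The strongest case against is that nothing in the article is wrong. Adjusting for the minimisation factors is a standard primary model that matches the allocation. The covariate list opens with the word *including*, and the detail is left to the analysis plan. The score's value beyond bulbar function, FVC and age is not in the document and may be near zero. All of this stands, and it makes the point an optional improvement.

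A reader might infer four stronger things, none of which the article supports:

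- *That the model is restricted to the four factors.* The list is open, and the unseen analysis plan may already add the score.
- *That the trial falls short of 85% power.* The drop to 82% (or 78% in the separate run) at 0.5 per SD appears only if 0.45 is read as conditional on the score. Sample size derives 0.45 from one-year group survival of 45% v 70%, an unadjusted contrast, and sizes on an unadjusted log-rank test. Under that reading (B) power without the score stays at about 88% at every strength, so the score is a bonus above target.
- *That there is no reserve.* The article allows 10% loss while expecting complete survival data. With all 108 patients, 108 × 0.638 = 68.9 deaths are expected, and Freedman's formula gives about 88% power.
- *That the gain is free.* It takes one more parameter, a chosen functional form and complete scores. It comes mainly from moving to a conditional hazard ratio further from 1, so the estimand shifts slightly.

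**Conclusion.** The point holds as a low-priority suggestion. The stated 85% power stands and the planned model is acceptable. Naming the non-bulbar screening ALSFRS-R score as a covariate would leave power about unchanged or raise it: by 0 to 3 points for an assumed residual log-hazard of 0 to 0.3 per SD, and by 4 to 7 points at 0.4 to 0.5. Nothing in the article says where in that range the score lies, or gives grounds for assuming a stronger effect.

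The conclusion rests on three assumptions: that the whole instrument is recorded at screening, not just its bulbar items; that its effect is roughly linear on the log-hazard; and that the analysis plan does not already include it. The first is reasonable, since Table 1 lists the whole instrument and bulbar function must be known before an allocation is returned.

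**What to change.** In the statistical analysis plan, name the screening ALSFRS-R score without its bulbar items as one continuous covariate in the primary Cox model, beside treatment and the four minimisation factors. Report the model without it as a sensitivity analysis. State how a missing score is handled, so that no patient leaves the primary analysis for lack of one. If the score is deliberately left out, record the reason. Settle this before anyone choosing the covariates has seen survival by arm.

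The cost is one line of wording and no new data. If each minimisation factor takes one parameter, which the article does not state, the model has six terms on about 62 deaths, or roughly ten deaths per term. The reported hazard ratio would be conditional on one more variable, and the report should say so.

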Diaphragm pacing (DP) is a technique initially developed for the treatment of respiratory muscle weakness in patients with spinal cord injury [10]. In this patient group it has allowed patients to reduce their time on mechanical ventilation or even remove the need for mechanical ventilation [11]. The NeuRX RA/4 System is a four channel percutaneous neuromuscular stimulation system. Intramuscular electrodes are implanted laparoscopically into the abdominal surface of the diaphragm, with leads tunnelled to an exit site on the abdomen. A small external stimulator delivers the stimulus pulses and provides respiratory timing. It is hypothesised that the potential benefits of DP in MND may come from a restoration of the coordination of respiration, lost as a result of upper motor neurone dysfunction, as well as conditioning of diaphragm muscle. In a healthy diaphragm slow twitch type I muscle fibres predominate. Disuse and suppression of the diaphragm activity, due to artificial ventilation, has been demonstrated to lead quickly to atrophy and to a predominance of fast type IIb muscle fibres [12]. The predominant type IIb muscles fibres lead to inefficient uncoordinated diaphragm contractions. In MND a similar process is likely to occur due to disuse (secondary to UMN dysfunction) and suppression of diaphragm activity due to NIV. DP may condition the diaphragm with a conversion back to efficient type I muscle fibres [13].

The anticipated benefits of DP in the MND patient group are: improved survival; improved quality of life; reduction in need for NIV; a less intrusive method of providing respiratory support compared to NIV.

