### Exclusion criteria

Participants must not have a prior NIV prescription or a pre-existing implanted electrical device such as pacemaker or cardiac defibrillator. Any underlying cardiac, pulmonary diseases or other disorders that would affect pulmonary function tests independently of MND/ALS, would increase the risk of general anaesthesia or adversely affect survival over the course of the study will be excluded. Significant decision making incapacity preventing informed consent by the subject due to a major mental disorder such as major depression, schizophrenia or dementia are exclusions. Others include marked obesity affecting surgical access to diaphragm or significant scoliosis/ chest wall deformity and the involvement in any respiratory trial that can influence the safety or outcome measures of this study within three months of the planned implantation of the device or during the year of follow up. A pre-existing diaphragm abnormality such as a hiatus hernia or paraoesophageal hernia of abdominal contents ascending into the thoracic cavity is an exclusion criterion. Patients with a forced Vital Capacity (FVC) < 50% predicted or SNIP < 30 cmH2O who are unable to perform FVC (bulbar patients) would be excluded – because of potential anaesthetic risk. A patient is eligible for the study if all the inclusion and none of the exclusion criteria are met.

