**Figure 2 F2:**
[figure not shown]
Participant flow within the trial.

At randomisation arrangements will be made for both NIV and DP insertion for trial participants. NIV initiation will occur as per usual practice at the study site as soon as possible following randomisation (within 1-2 weeks). For those randomised to the DP arm, a provisional date for implantation will be allocated at randomisation (within 2-3 weeks). Patients should be able to use NIV prior to implantation. NIV should be available to patients in the anaesthetic recovery room post implantation of the device.

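### Survival split by NIV tolerance conditions on a post-randomisation variable; keep it descriptive and base subgroup inference on baseline bulbar function

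*Protocol article*

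**What the plan says.** The Data analysis section of the protocol article defines the primary outcome as time from randomisation to death, analysed by Cox regression on treatment and the minimisation factors. It then adds, as a secondary analysis: "we will also report survival separately for patients who are NIV tolerant and those who are NIV intolerant". It gives no definition of tolerance, no time of classification and no caution about interpretation.

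Other sections fix when tolerance can first be known:

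- Exclusion criteria: "Participants must not have a prior NIV prescription".
- Text after Figure 2: "NIV initiation will occur as per usual practice at the study site as soon as possible following randomisation", with one to two weeks given. Implantation in the DP arm is provisionally within two to three weeks.
- Same place: "Patients should be able to use NIV prior to implantation".
- Method of randomisation: "The participant will be informed of their treatment allocation within a week of randomisation either by phone or letter". The minimisation factors are bulbar function, FVC, age and sex.
- Background: the anticipated benefits of DP include "reduction in need for NIV". Patients with marked bulbar compromise are said not to tolerate NIV and had no significant survival benefit in the earlier NIV trial. Claustrophobia and mask problems are given as further causes of intolerance.

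**The concern.** Randomisation makes the arms comparable within any subgroup defined by something fixed before allocation. It gives no such guarantee for a subgroup defined by what happens afterwards. If DP, or knowledge of being allocated to DP, changes who is classed as tolerant, and tolerance tracks prognosis, then tolerant DP patients and tolerant controls are different kinds of patient. The same holds for the intolerant. A difference in survival between arms can then appear with no treatment effect, or a real effect can be hidden.

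The stake is interpretive. Patients in whom NIV fails are a main part of the stated rationale for DP, and this is the only subgroup survival analysis that the article names. Readers would naturally take it as evidence on whether DP helps those patients.

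**Working it through.** **1. Can tolerance be a baseline factor?** No. Participants enter without an NIV prescription, and NIV begins after randomisation in both arms. Table 1 lists NIV use at screening, but with prior NIV excluded that entry cannot measure tolerance. No later definition can turn it into a pre-randomisation variable.

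**2. Could it differ by arm?** Possibly. Allocation is disclosed within a week, at about the time NIV starts. Implantation follows at two to three weeks, and DP is expected to lower the need for NIV. These are reasons to allow for an effect; they do not show one.

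**3. Is it related to prognosis?** The Background links intolerance to bulbar compromise and to the lack of a significant survival benefit from NIV.

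**4. The plan's own figure.** There is none for this analysis. The sample size reproduces:

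- Simpson average survival, control: (0.45 + 4×0.20 + 0.10)/6 = 0.225. DP, each term raised to the power 0.45: 0.499.
- Probability of death: 1 − (0.225 + 0.499)/2 = 0.638.
- Freedman events: (1.960 + 1.036)² × (1.45/0.55)² = 62.4.
- N: 62.4/0.638 = 97.8; divided by 0.90 = 108.6, against 108 stated. Power at 108 is 84.8%. Expected deaths: 108 × 0.90 × 0.638 = 62.

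**5. Illustration A (assumed inputs, no DP effect).** 30% are intolerant with twice the hazard, and 10%, 20% or 30% of otherwise tolerant DP patients are classed with the intolerant. At the start, the hazard ratio in the intolerant class is:

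- 10%: (0.30×2 + 0.07×1)/0.37 ÷ 2 = 0.91
- 20%: (0.30×2 + 0.14×1)/0.44 ÷ 2 = 0.84
- 30%: (0.30×2 + 0.21×1)/0.51 ÷ 2 = 0.79

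Over follow-up (planning survival, censoring uniform over 12 to 30 months) the high-risk patients die first, and simulated Cox estimates fall to 0.86, 0.79 and 0.73.

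**6. Illustration B (assumed inputs, no DP effect).** 12-month survival is 45% in both arms, log-hazard frailty has SD 0.8, and tolerance is less likely with worse prognosis (logit slope 0.5 to 1.0 per SD). About 67–69% of controls are tolerant.

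| Effect of DP on tolerance (logit) | Tolerant on DP | HR, all | HR, tolerant | HR, intolerant |
|---|---|---|---|---|
| none | 67–69% | 1.00 | 1.00 | 1.00 |
| −1 | 46–47% | 1.00 | 0.90–0.94 | 0.89–0.93 |
| +1 | 83–85% | 1.00 | 1.05–1.09 | 1.06–1.11 |

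Both subgroups move the same way while the whole-trial ratio does not, because patients of intermediate prognosis change class.

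**7. Precision.** Power is Φ(√d × 0.55/1.45 − 1.96) for d deaths. Sharing the 62 deaths in proportion to an assumed tolerant share of 50–80%, the tolerant group has 31–50 deaths (56–76% power at a hazard ratio of 0.45) and the intolerant group 31–12 deaths (56–27%).

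**8. Precision of a bulbar interaction.** With a favourable even split of deaths, SE = √(4/31 + 4/31) = 0.51, against √(4/62) = 0.25 for the overall effect. The 95% interval for a ratio of hazard ratios of 1 is exp(±1.96 × 0.51), about 0.37 to 2.7.

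**The case against.** The strongest reply is that the analysis is secondary, that the article undertakes only to report survival and names no test, hazard ratio or claim, and that definition and timing belong to an analysis plan not shown here. Tolerance judged at NIV initiation would largely precede any direct action of DP, since implantation comes later and pacing builds up over the first month. That stands as a reason for a moderate grading. It does not remove the point: even an early classification follows randomisation and is made with allocation known.

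Four stronger readings are tempting and are not supported:

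- *That a bias of known size has been shown.* Every input to both illustrations is assumed, and there is no bias of this kind if DP and knowledge of allocation leave tolerance unchanged.
- *That less need for NIV means intolerance.* Illustration A depends on classing patients who do without NIV as intolerant; the article nowhere equates the two.
- *That intolerance means something different in each arm because DP patients should be able to use NIV before surgery.* The sentence states no definition of tolerance and no consequence of failing, so this is conjecture.
- *That early deaths which cannot be classified bias the comparison of arms.* They affect both arms; the comparison is distorted only if they do so unequally, which nothing here establishes.

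Noise would also swamp the illustrated shifts. If 30% are intolerant with twice the hazard, average survival in that group is (0.45² + 4×0.20² + 0.10²)/6 = 0.06, so about 30 of 32 patients die. The 95% interval around a null hazard ratio is then exp(±1.96 × √(4/30)), or 0.49 to 2.05. The risk is misreading a small table.

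**Conclusion.** The concern holds in a limited form, at moderate severity. Tolerance as a post-randomisation variable is established by the article's own entry rule and timetable. That it tracks prognosis is supported by the Background. That DP alters it is plausible but unproven. Between-arm comparisons within the two groups are therefore unprotected by randomisation, and the direction and size of any distortion are unknown; the illustrated ratios are not estimates for this trial. A reader might infer that the trial's main result is compromised. It is not: the primary comparison runs from randomisation in all patients, and the sample size of 108 does not depend on this split.

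**What to change.** 1. Make the inferential subgroup analysis a treatment-by-baseline-bulbar-function interaction in the primary Cox model. Bulbar function is measured at screening, is a minimisation factor and is already a covariate, so this adds one term and no data. State that it is only a partial proxy, since claustrophobia and mask problems also cause intolerance, and that its power is low. It answers a related question, not the identical one.

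2. Keep the NIV-tolerance split only as a descriptive, non-causal summary. Fix one definition of tolerance, applied by the same rule and at the same early time point in both arms. Count survival from that point, and report by arm the deaths and losses before it.

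3. Check what the data allow before fixing the time point. Diaries run from NIV initiation, but the first scheduled visit common to both arms is at 2 months, and the article does not establish that an equal classification before implantation is feasible. At 2 months DP is already in use, which is a further reason for the descriptive label.

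The cost is analysis-plan wording, settled before survival by tolerance is tabulated. The primary analysis and sample size do not change.
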